# SYNOPSIS

**LAY SUMMARY**

Administrative claims databases and electronic health records (EHR) are valuable resources for pregnancy research since pregnant women are excluded from randomized clinical trials (RCTs). In general, direct measures of gestational age are not available in claims databases and EHRs and an algorithm based on data available must be developed and validated in order to define the entire pregnancy episode from start to pregnancy outcome.

Our aim is to develop an algorithm to define pregnancy episodes for a network of population-based databases using the OMOP Common Data Model (CDM). We will attempt to identify all possible pregnancy outcomes with the algorithm, including live birth (at least one), stillbirth, delivery record only, trophoblastic disease, ectopic pregnancy, induced abortion and spontaneous abortion. Pregnancy episode start dates will be inferred with various pregnancy markers such as last menstrual period and nuchal ultrasound dates.

Our publication strategy will involve disseminating the algorithm methods and results from the electronic profile validation through a journal which focuses on epidemiology and/or drug safety. The validation should provide insight into the accuracy of various operating characteristics of the algorithm, such as start date inferral and outcome assignment. Validation results will be presented separately for each database in one publication in order to highlight the fact that it was possible to use one algorithm for all databases converted to the CDM at Janssen.

INTRODUCTION

Administrative claims databases and electronic health records (EHR) are valuable resources for pregnancy research since pregnant women are excluded from randomized clinical trials (RCTs). In general, direct measures of gestational age are not available in claims databases and EHRs and an algorithm based on data available must be developed and validated in order to define the entire pregnancy episode from start to pregnancy outcome.

A study has not been performed that has attempted to accurately define pregnancy episodes including pregnancy start date on a network of population-based databases from the US and the UK using the OMOP Common Data Model (CDM). Using the CDM allows us to create one set of pregnancy concepts and one algorithm that can be applied to all data sources converted to the CDM, despite disparate native source code dictionaries and data structures found within each database. Additionally, prior observational data studies in which pregnancy episodes were identified have either been based upon populations that were potentially not generalizable or have only examined live birth outcomes. It is important to examine all possible outcomes (e.g. spontaneous and induced abortion, stillbirth, ectopic pregnancies etc.) as patient characteristics, prescribing patterns etc. in these populations may be dissimilar from patterns in pregnancies ending in live births.

OBJECTIVES

Our aim is to define pregnancy episodes and their outcomes (all possible outcomes including live births, stillborn, spontaneous and induced abortion, ectopic pregnancies etc.) within 3 US-based administrative claims databases: Truven MarketScan Commercial Claims and Encounters (CCAE), Truven MarketScan Multi-state Medicaid (MDCD), and the Optum ClinFormatics (Optum) database and the Clinical Practice Research Datalink (CPRD) which is a UK based general practice electronic health record.

These will be validated with review of 50 CPRD and 50 Optum randomly drawn pregnancy episodes from each outcome (6 outcomes X 50 X 2) for a total of 600 profiles by clinical personnel. Proportion of episodes by outcome which refer to an actual pregnancy, proportion of episodes by outcome with correct outcome, and proportion of episodes by outcome with correct start date (or plausible start date if inferred) for each database will be determined.

OVERVIEW OF STUDY DESIGN

This study follows a retrospective cohort design. 7 pregnancy episode outcome cohorts will be created and characterized from women with any pregnancy markers or outcomes:

- Live birth (at least one)
- Stillbirth
- Delivery-Live birth or stillbirth
- Trophoblastic Disease
- Ectopic pregnancy
- Induced abortion
- Spontaneous abortion

Women are allowed multiple pregnancy episodes.

STUDY POPULATION

Women between 12 and 55 years of age who were enrolled continuously during their pregnancy episode defined by the algorithm within the 4 databases with any pregnancy markers or outcomes.

STATISTICAL METHODS

For each pregnancy episode, we will determine the beginning and end of the pregnancy episode and determine the outcome.

ABBREVIATIONS

| IRB | Institutional Review Board |
| --- | --- |
| MedDRA | Medical Dictionary for Regulatory Activities |
| CCAE | Truven MarketScan Commerical Claims and Encounters |
| MDCR | Truven MarketScan Medicare Supplemental Beneficiaries |
| MDCD | Truven MarketScan Multi-state Medicaid |
| Optum | Optum ClinFormatics |
| OMOP | Observational Medical Outcomes Partnership |
| CDM | Common Data Model |
| CI | Confidence interval |
| CPRD | Clinical Practice Research Datalink |

## INTRODUCTION

### Background

Administrative claims databases and electronic health records (EHR) are valuable resources for pregnancy research since pregnant women are excluded from randomized clinical trials (RCTs). In general, direct measures of gestational age are not available in claims databases and EHRs and an algorithm based on data available must be developed and validated in order to define the entire pregnancy episode from start to pregnancy outcome.

Many algorithms have been documented in the literature. Hornbrook et al. created an algorithm to identify pregnancy episodes and outcomes from Kaiser Permanente Northwest automated US healthcare records [[1](#_ENREF_1)]. Beginning and end of the pregnancy episode along with a range of outcomes including live birth, spontaneous and induced abortion, stillbirth etc. were determined for each pregnancy using condition and procedure codes from outpatient and inpatient data, laboratory tests and pharmacy records. In their electronic health data, gestational age was available for some pregnancies in hospital discharge data, otherwise gestational age of the infant was estimated using national median gestational age by outcome type. Percent agreement between their algorithm and medical records review ranged from 91-98% for outcome, gestational age and outcome date. With their algorithm, 68% of all pregnancy episodes defined ended in a live birth, 17% ended in induced abortion, 13% ended in spontaneous abortion, 1% ended in ectopic pregnancy and <1% ended in stillbirth, trophoblastic pregnancy, live or stillbirth or unknown outcomes.

Margulis et al. determined with a population-based cohort of mother-child pairs in British Columbia that subtracting 245 days from live births with pre-term delivery ICD-9 codes and 273 days for those without provided best estimates of the beginning of pregnancy as compared to the hospital discharge record (68.1% of estimated gestational age at birth were within 1 week of the hospital discharge estimate) [[2](#_ENREF_2)]. A second algorithm in this effort attempted to determine beginning of pregnancy with screening test claims such as alpha fetoprotein in live births usually administered within narrow gestational-age windows (45.4% of estimated gestational age at birth were within 1 week of the hospital discharge estimate).

Two UK-based studies involving CPRD or The Health Improvement Network (THIN) which are both drawn from general practice data in the UK defined pregnancy episodes by determining the appropriate end of pregnancy marker and mapping it to the first found early pregnancy marker [[3](#_ENREF_3), [4](#_ENREF_4)]. A more recent study utilizing THIN data used last menstrual period (LMP) date which was present for 50.8% of pregnancies to determine beginning of pregnancy [[5](#_ENREF_5)].

A study has not been performed that has attempted to accurately define pregnancy episodes including pregnancy start date on a network of population-based databases from the US and the UK using the OMOP Common Data Model. Using the CDM allows us to create one set of pregnancy concepts and one algorithm that can be applied to all data sources converted to the CDM, despite disparate native source code dictionaries and data structures found within each database.

Additionally, prior observational data studies examining pregnancy using the types of algorithms described above have either been based upon populations that were not generalizable or have only examined live birth outcomes [[6-8](#_ENREF_6)]. It is important to examine all possible outcomes (e.g. spontaneous and induced abortion, stillbirth, ectopic pregnancies etc.) as patient characteristics, prescribing patterns etc. in these populations may be dissimilar from patterns in pregnancies ending in live births.

### Overall Rationale for the Study

## STUDY OBJECTIVES

### Primary Objective(s)

Our primary objective is to evaluate an algorithm that will determine pregnancy episodes (pregnancy start to end) and outcomes for the episodes (including outcomes other than live birth) in all applicable Janssen network databases.

### Secondary Objective(s)

Hypothesis:

This pregnancy study is descriptive in nature and does not involve any statistical tests.

## OVERVIEW OF STUDY DESIGN

### Study Design

This study follows a retrospective cohort design. 7 pregnancy episode outcome cohorts will be created and characterized from women with any pregnancy markers or outcomes:

- Live birth (at least one)
- Stillbirth
- Delivery-Live birth or stillbirth
- Trophoblastic Disease
- Ectopic pregnancy
- Induced abortion
- Spontaneous abortion

Women are allowed multiple pregnancy episodes and the unit of analysis will be the pregnancy episode. Valid pregnancy outcomes for each patient will be chosen using an algorithm that utilizes an outcome assessment hierarchy, i.e. live births are assessed for validity first for each patient, any that are too close to another live birth are discarded. Still births for the same patient are then assessed to see if they are too close to all prior assessed live births and any other valid still births etc. Start dates will be assigned using pregnancy markers in a hierarchical fashion also (last menstrual period date records considered as start of pregnancy first, next considered are gestational age estimate records, etc.) See page 12 for a full description of the algorithm.

In medical practices, pregnancy episodes traditionally begin with the last menstrual period date and end with the birth outcome date as defined by the algorithm. The first trimester is defined as week 1-13, 2^nd^ trimester week 14-26 and 3^rd^ trimester week 27-40. For our episodes, the first two weeks of the first trimester will be defined as a pre-exposure period as conception most likely does not happen prior to this time.

### Study Design Rationale

A retrospective cohort design will allow pregnancies to be identified at pregnancy start as defined above and followed longitudinally to the birth outcome.

## STUDY POPULATION

### Patient Selection

NOTE: All subject data for this study are being collected using databases only.

This analysis will be conducted within 3 US-based administrative claims databases: Truven MarketScan Commercial Claims and Encounters (CCAE) which provides data from 1/2000-10/2014, Truven MarketScan Multi-state Medicaid (MDCD) (data available from 1/2006-12/2013), and the Optum ClinFormatics (Optum) database (data available from 10/2005-9/2014). The analysis will also be conducted within the Clinical Practice Research Datalink (CPRD), which is a UK based general practice electronic health record which provides data from 9/1987-7/2014. All databases are transformed to the OMOP Common Data Model (CDM) v4. Details about the OMOP CDM are available at: <http://omop.org/CDM>. One standard analysis program will be developed for this protocol, and executed consistently across all databases using the OMOP CDM.

The transformation of CPRD data into the OMOP CDM V4 and the validation performed at Janssen has been described previously [[9](#_ENREF_9)]. Validation of the conversion of Read codes classified as conditions to SNOMED-CT results from the above publication are as follows: “99.9% of condition records in the CDM condition occurrence file and 98.9% of condition terms were mapped to the SNOMED-CT dictionary. The top 100 occurring conditions in the CPRD CDM made up 47% of the condition data and all were mapped and classified correctly. 97.7% of procedure records in the procedure occurrence file and 86.4% of procedure terms were mapped to the SNOMED-CT dictionary. The top 100 occurring procedures in the CPRD CDM made up 68.5% of the procedure data and all were mapped and classified correctly. The final observation file with all 3 observation record sources (lifestyle/clinical, lab and Read code observation data) had 94.2% of observations records and 75.2% of observation terms mapped to either the LOINC or SNOMED-CT dictionaries. The top 100 occurring observations in the CPRD CDM made up 60% of the observation data and all were mapped and classified correctly except four unmappable codes from the lifestyle/clinical data.” Also, prevalences for selected conditions across CPRD raw and CDM data were equivalent and **r**esults between the replication raw data and CDM study agreed for conditions, demographics and lifestyle data. [[9](#_ENREF_9)]. Additionally, a commentary piece by Rijnbeek describes advantages and potential limitations of the CPRD CDM conversion performed by [name] et al [[10](#_ENREF_10)].

All data available within all data sources will be considered for use for construction of the pregnancy episodes. All analyses are retrospective based on existing de-identified patient-level data, and will not require prospective data capture or patient re-identification for source record verification or other purposes. Cohorts will be constructed from inclusion criteria specified below.

#### Inclusion Criteria

Women between 12 and 55 years of age who were enrolled continuously during their pregnancy episode determined from pregnancy markers or outcomes within the 4 databases will be included in the study. This age group was chosen to detect pregnancies amongst girls with earlier menarche as well as pregnancies in older women (primarily due to extension of fertility with medical interventions) [[1](#_ENREF_1)].

#### Exclusion Criteria

Delete episodes which end after or start prior to the patient’s valid observation period.

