1. If AFP date-123 exists between (larger of maximum term allowed subtracted from outcome date or prior outcome date plus retry count) and minimum term allowed subtracted from outcome date then AFP date-123 becomes the pregnancy start date.
2. If there are more than one AFP records in the allowed time window, use the first so as to use the AFP date that is most likely the recommended date in clinical guidelines rather than a repeat test.

**Step 5:** Outcome specific estimates:

1. If at least one PREM (premature term pregnancy), POSTT (post term pregnancy) or FT (full term pregnancy) record exists between (larger of maximum term allowed subtracted from outcome date or prior outcome date plus retry count) and 30 days after outcome date then categorize pregnancy as PREM, POSTT or FT.
2. If combinations of PREM, POSTT, FT records exist in this time window, categorize pregnancy in this order: 1) PREM if present, 2) POSTT if present, 3) FT if present.
3. Based on Table 4, choose an outcome specific gestational age estimate based on outcome and term and subtract from outcome date to obtain a pregnancy start date. If prior outcome date plus retry count is greater than outcome date minus outcome specific gestational age estimate then pregnancy start date becomes prior outcome date plus retry count.

**Step 6**: Choose final pregnancy start date:

1. Choose the best pregnancy start date (first one assigned in steps 1-5).
2. If a PCONF (pregnancy confirmation), AGP (antenatal GP visit) or OTEST (other pregnancy test) category records exist between (larger of maximum term allowed subtracted from outcome date or prior outcome date plus retry count) and minimum term allowed subtracted from outcome date and is prior to the best start date as calculated in the prior 5 steps then the first found PCONF, AGP or OTEST becomes pregnancy start date.

Table 4 provides outcome specific gestational age estimates for all outcomes for premature, post and full term pregnancies. These outcome specific gestational age estimates were obtained from Hornbrook et al.[[1](#_ENREF_1)] and Margulis et al. and were validated by in-house clinical experts and should represent average gestational times for the outcomes and terms.

| **Table 4: Outcome Specific Gestational Age Estimates in Days** | | | | |
| --- | --- | --- | --- | --- |
| **Outcome** | **PreTerm** | **PostTerm** | **FullTerm** | **NoData** |
| **LB** | 245 | 285 | 280 | 280 |
| **SB** | 196 | 285 | 280 | 196 |

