### Statistical Analysis Plan

#### Descriptive Analyses

Counts of pregnancy episodes and distribution of outcomes will be produced for this study. Also distributions of pregnancy terms by outcome will be reviewed.

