#### Sensitivity and Other Supplementary Analyses

No pre-specified sensitivity analysis will be performed.

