## STUDY LIMITATIONS

Truven CCAE and Medicaid and Optum databases only capture information reported through the payer, so any non-reimbursable exposures or health service utilization from other sources may not be observed in these data sources. In CPRD the general practices receive information from patient specialist visits but are not required to enter the data if it is not needed to inform future patient care. Births that do not occur in an inpatient setting most likely will not be captured in a claims database. Entire pregnancy episodes may not be captured by our algorithm, especially miscarriages occurring early in the pregnancy that require no medical care. Misclassification of outcomes could occur due to ambiguous outcome source codes.

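### Requiring the whole episode to be observed drops recorded births more often than recorded abortions, so the planned outcome distribution is tilted toward early losses relative to the outcomes the algorithm records.

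*Protocol*

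**What the plan says.** Inclusion Criteria admits women "who were enrolled continuously during their pregnancy episode determined from pregnancy markers or outcomes". Exclusion Criteria adds the instruction "Delete episodes which end after or start prior to" the woman's valid observation period. Together they keep an episode only if its full inferred length is observed.

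That length depends on the outcome. In Table 4 the live-birth row reads "LB | 245 | 285 | 280 | 280" (preterm, post-term, full term, no term data). Induced and spontaneous abortion are set at 70 days and ectopic pregnancy at 56, whatever the term.

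Under Descriptive Analyses the protocol states: "Counts of pregnancy episodes and distribution of outcomes will be produced for this study". It describes no common look-back, no weighting and no count of deletions by outcome. Under Sensitivity and Other Supplementary Analyses it states: "No pre-specified sensitivity analysis will be performed". Study Limitations mentions incomplete capture, "especially miscarriages occurring early in the pregnancy that require no medical care", but not loss through the enrolment rule.

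**The concern.** A woman whose live birth is recorded 200 days after her enrolment begins will usually lose that episode, because its inferred start falls before enrolment. A woman with a miscarriage recorded on the same day will usually keep hers. This is left truncation that depends on the outcome being tabulated.

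The protocol argues that outcomes other than live birth need to be studied, and the outcome distribution is one of its few planned descriptive results. If the rule alone shifts that distribution by several percentage points, readers cannot separate the effect of the enrolment requirement from what the algorithm found. Short observation makes the shift larger, so databases whose women are observed for different lengths of time would be shifted by different amounts.

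**Working it through.** The protocol gives no retention figure to reproduce, so the check is a simple truncation model.

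**Inputs from the protocol**
- Episode length L (Table 4, no term data): live birth 280 days, induced and spontaneous abortion 70, ectopic 56, stillbirth 196.
- Illustrative mix before deletion, from the US health-plan algorithm cited in Background: "68% of all pregnancy episodes defined ended in a live birth, 17% ended in induced abortion, 13% ended in spontaneous abortion", and 1% ectopic. The remaining 1% is given L = 196.

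**Assumptions**
- The cited mix is the true mix of recorded outcomes.
- Outcome dates are uniform over an observation window of T days.
- T is not given per woman, so a range is shown.

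**Formula.** P(kept) = 1 − L/T. Share after deletion = share × P(kept), divided by the sum over outcomes.

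**Example, T = 730 days**
- Live birth: 1 − 280/730 = 61.6%; 0.68 × 0.616 = 0.419.
- Induced abortion: 1 − 70/730 = 90.4%; 0.17 × 0.904 = 0.154.
- Spontaneous abortion: 0.13 × 0.904 = 0.118.
- Ectopic: 0.01 × 0.923 = 0.009. Remainder: 0.01 × 0.732 = 0.007.
- Sum 0.707. Live-birth share = 0.419/0.707 = 59.3%.

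| T | Live births kept | Abortions kept | Live-birth share (68% before) | Induced abortion share (17%) | Spontaneous abortion share (13%) |
|---|---|---|---|---|---|
| 1 year (365 days) | 23.3% | 80.8% | 38.3% | 33.2% | 25.4% |
| 2 years (730) | 61.6% | 90.4% | 59.3% | 21.7% | 16.6% |
| 3 years (1095) | 74.4% | 93.6% | 62.9% | 19.8% | 15.1% |
| 5 years (1826) | 84.7% | 96.2% | 65.2% | 18.5% | 14.2% |
| 10 years (3650) | 92.3% | 98.1% | 66.7% | 17.7% | 13.5% |

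**Unequal windows.** If window length is exponential with mean m, P(kept) = exp(−L/m). The live-birth share is then 54.6%, 61.5%, 63.8%, 65.5% and 66.8% for means of 1, 2, 3, 5 and 10 years.

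**Other episode lengths.** Take live births at 280 days and the longest non-birth terms in Table 2 (induced abortion 168, spontaneous abortion 133, ectopic 84). The live-birth share is still down to 62.3% at 2 years and 64.7% at 3. The order of live birth and induced abortion reverses only near the Table 2 extremes, with births near 161 days and induced abortions near 168.

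**Does a common look-back remove the dependence?** Steps 1 to 4 and the marker adjustment in Step 6 confine start dates to the maximum term in Table 2, which is at most 301 days. The Step 5 estimates are at most 285 days (Table 4). An outcome dated at least 301 days after observation starts therefore cannot be deleted for its start date. In this model every outcome is then kept with the same probability, 1 − 301/T, and the mix is recovered. The fraction kept is 58.8% at 2 years (70.7% under the present rule) and 17.5% at 1 year (41.4%).

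**The case against.** The strongest reply is that the rule is deliberate and the affected table is secondary. The primary objective is to evaluate an algorithm that defines complete episodes, and an episode whose start is unobserved cannot be searched for early markers. The main published result is the profile validation, reported by outcome. The protocol nowhere says that the outcome distribution estimates population shares. This stands as a reason to keep the rule for building episodes. It does not make the distribution interpretable when the rule has changed its composition without disclosure.

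Second, other features act the other way. Early miscarriages without care go unrecorded, as the limitations say, and the 42-day rule-outs remove some ectopic and spontaneous abortion records. A reader might infer that births are understated relative to all pregnancies; the documents do not support that. In the fixed-window model the live-birth share returns to 68% if only a fraction c of spontaneous abortions is recorded. At 2 years, c = (0.32 × 0.616 − 0.17 × 0.904 − 0.01 × 0.923 − 0.01 × 0.732)/(0.13 × 0.904), about 23%. At 3 years it is about 50%, and at 5 years about 71%. Induced abortion would still be too high: 0.154/(0.419/0.68) = 24.9% at 2 years against 17%. An offset of unknown size narrows the claim but does not correct the table.

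Third, the size depends on assumptions. The 1-year figure of 38% requires every woman to have exactly one year of observation; exponential windows with a 1-year mean give about 55%. At 5 years both models give a loss of about 3 points. The starting mix is itself the output of another algorithm.

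Fourth, a reader might infer that the claims databases and CPRD will show spurious differences. The protocol gives calendar spans, not enrolment per woman, and says that no explicit comparisons across databases will be made. The point is therefore conditional: if observation length differs, so does the distortion.

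**Conclusion.** The point holds for the planned outcome distribution, relative to the outcomes the algorithm records. With Table 4 lengths the direction is the same for any finite observation period: births are under-retained, and induced and spontaneous abortions are over-represented. The size is not fixed by the documents. Under the assumptions above the loss in live-birth share is about 9 points with fixed 2-year windows (about 6 with exponential windows of that mean), 3 points at 5 years and 1 point at 10.

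The conclusion does not extend to the validation. Those proportions are computed within outcome and are not directly distorted. Nor does it establish a net bias against all pregnancies, or an actual difference between databases. It should be addressed because the correction is cheap and the protocol neither corrects nor discloses the selection, but it does not undermine the primary objective.

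**What to change.** Under Descriptive Analyses, alongside the planned distribution, add one restricted to outcomes dated at least 301 days (the largest maximum term in Table 2) after the start of the woman's observation, with the same rule for every outcome. Report the number of episodes deleted by outcome in each database. Add a sentence to Study Limitations saying that the full-observation rule removes long episodes more often than short ones. Episode building and validation stay as they are.

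The cost in text is small: a sentence in each section and one extra table. The cost in data is larger. The added table loses every outcome in the first 301 days, including stillbirths, preterm births and some term births as well as abortions and ectopic pregnancies. Where observation is short, little remains. The table describes women with at least 301 days of prior observation, and it matches the mix of all recorded outcomes only if that mix does not change with time since enrolment. It is therefore best shown beside the planned distribution and not in its place.
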